### Data collection

The following instruments will be used (see Table 1, which depicts the timeline for data collection).

*Smoking Habit Questionnaire* [40]. A 59-item questionnaire assessing participant sociodemographic characteristics (e.g., sex, age, education) and smoking-related behaviors: current and past use of cigarettes and other tobacco products; age of smoking onset; previous quit attempts or cigarette reduction; reasons for quitting in previous attempts; past and current diseases; symptoms and discomforts related to smoking; alcohol, coffee/tea, and medication use; desire to quit smoking; desire to participate in the treatment; expectations about treatment; and stages of change [41].*The Fagerström Test for Cigarette Dependence* (FTCD) [42, 43]. Includes 6 items to assess cigarette dependence.*Structured Interview Assessment of DSM-5 Diagnostic Criteria for Tobacco Use Disorder*. This is a diagnostic interview developed following the DSM-5 criteria to assess tobacco use disorder.*Beck Depression Inventory-II* (BDI-II) [44, 45]. This is a 21-item self-report scale measuring current depressive symptoms.*Snaith-Hamilton Pleasure Scale* (SHAPS) [46, 47]. This 14-item scale assesses 4 domains of hedonic experience: interest/hobbies, social interaction, sensory experience, and satisfaction with food/drink.*Minnesota Nicotine Withdrawal Scale* (MNWS) [48]. This 8-item scale measures nicotine withdrawal symptoms (depression, insomnia, irritability/frustration/anger, anxiety, difficulty concentrating, restlessness, increased appetite/weight gain) and craving (smoking urgency).*Self-Efficacy/Smoking Temptation Scale* [49]. This 9-item instrument assesses the temptation to smoke in positive affect/social situations, negative affect situations, and habit situations.*Questionnaire of Smoking Urges* (QSU) [50]. The QSU consists of 10 items assessing craving to smoke. It has two factors: (1) the intention or desire to smoke, and (2) expectations of negative reinforcement or improvements through smoking.*Multidimensional Scale of Perceived Social Support* (MSPSS) [51, 52]. This 12-item self-report scale assesses perceived social support from family, friends, and others.*The 20-item Partner Interaction Questionnaire* (PIQ-20) [53]. This questionnaire assesses social support for adults wishing to stop smoking.*Environmental Reward Observation Scale* (EROS) [54, 55]. This 10-item self-report assesses the amount and availability of environmental reward.*Behavioral Activation for Depression Scale Short Form* (BADS-SF) [56, 57]. This scale includes 9 items assessing activation and avoidance behaviors.*International Physical Activity Questionnaire Short Form* (IPAQ-SF) [58]. This 7-item questionnaire measures participation in vigorous- and moderate-intensity physical activity and sedentary behaviors over the past seven days.*Satisfaction with Life Scale* (SWLS) [59, 60]. A scale designed to measure global life satisfaction through 5 items.*The visual-analogue scale of the EuroQoL-5D Quality of Life Questionnaire* (EQ-5D) [61]. It assesses health status perception on a scale ranging from 0 to 100.*Questionnaire about the use of smartphones and Apps*. An ad hoc questionnaire will be designed to collect information about the use of smartphones (i.e., frequency, time of use, type of use) and Apps (i.e., frequency of use, hours of use, types of Apps).*User Version of the Mobile Application Rating Scale* (uMARS) [62, 63]. This is a 20-item measure that includes 4 objective quality subscales (engagement, functionality, aesthetics, and information quality) and one subjective quality subscale.*System Usability Scale* [64, 65]. This 10-item instrument assesses the usability of a system (software interfaces, webpages, and mobile apps), alternating positive and negative statements.*Self-report of smoking*. Participants will track their smoking behavior by registering each cigarette, time when they smoked, the situation, and how much pleasure they experience with each cigarette on a scale from 0 to 10.*Assessment of Carbon monoxide in expired air (CO).* The iCOquit^®^ Smokerlyzer^®^ (Bedfont Scientific Instruments Ltd, Sittingbourne, Kent, United Kingdom) will be used to measure carbon monoxide (CO) in expired air. This is a personal device designed for the remote assessment of carbon monoxide, providing a particles per million (ppm) reading [66, 67]. Participants who self-report 7-day point-prevalence abstinence at any time-point will receive a CO monitor device via postal mail, together with detailed instructions for app installation, Bluetooth pairing, and CO measurement. Research staff will schedule a brief video call to assist and supervise the CO collection.*End-of-treatment questionnaire*. This self-report collects information about quit date, confidence in remaining abstinent, physical, and psychological improvements since the beginning of treatment, and possible negative effects of the intervention.*Client Satisfaction Questionnaire* (CSQ-8) [68, 69]. This 8-item instrument measures overall satisfaction with treatment services and will be administered at the end of treatment.*Follow-up questionnaire*, in which tobacco related information is collected at 3-, 6-, and 12- month post-treatment.

**Fig. 2 Fig2:**
[figure not shown]
CONSORT diagram of trial progression [70]

**Table 1 Tab1:** Timeline for data collection through the trial

		STUDY PERIOD				
	Enrollment	Allocation	EOT	3-M	6-M	12-M
**ENROLLMENT**						
Eligibility screen	X					
Informed consent	X					
Allocation		X				
**INTERVENTIONS**						
TC 1 High intensity contact						
TC 2 Low intensity contact						
TC 3 Only app						
**ASSESSMENTS**						
Smoking Habit Questionnaire		X				
DSM-5 Diagnostic Criteria for TUD		X				
FTCD		X				
BDI-II		X	X	X	X	X
SHAPS		X	X	X	X	X
MNWS		X	X	X	X	X
Self-Efficacy/Temptation Scale		X	X	X	X	X
QSU		X	X	X	X	X
MSPSS		X	X	X	X	X
PIQ-20		X	X	X	X	X
EROS		X	X	X	X	X
BADS Short Form		X	X	X	X	X
IPAQ-SF		X	X	X	X	X
SWLS		X	X	X	X	X
EuroQoL-5D		X	X	X	X	X
Use of smartphones and Apps Questionnaire		X				
CSQ-8			X			
SUS			X			
uMARS			X			X
***Primary outcome***						
7-days point prevalence abstinence						X
***Secondary outcomes***						
CSQ-8			X			
7-days point prevalence abstinence			X	X	X	

TC = Treatment Condition; EOT = End of treatment; 3-M = 3 months follow-up; 6-M = 6 months follow-up; 12-M = 12 months follow-up; TUD = Tobacco Use Disorder; FTCD = Fagerström Test for Cigarette Dependence; BDI-II = Beck Depression Inventory-II; SHAPS = Snaith-Hamilton Pleasure Scale; MNWS = Minnesota Nicotine Withdrawal Scale; QSU = Questionnaire of Smoking Urges; MSPSS = Multidimensional Scale of Perceived Social Support; PIQ-20 = Partner Interaction Questionnaire; EROS = Environmental Reward Observation Scale; BADS-SF = Behavioral Activation for Depression Scale Short Form; IPAQ-SF = International Physical Activity Questionnaire Short Form; SWLS = Satisfaction with Life Scale; EQ-5D = EuroQoL-5D Quality of Life Questionnaire; SUS = System Usability Scale; uMARS = User Version of the Mobile Application Rating Scale; CSQ-8 = Client Satisfaction Questionnaire

#### Primary outcome

Smoking abstinence in the three study conditions will be self-reported and biochemically validated using carbon monoxide (CO) in exhaled air [71], using the iCOquit^®^ Smokerlyzer^®^. These devices will be mailed to participants. A participant will be classified as abstinent from smoking if they report not smoking, not even a puff, in the previous 7 days and provide a CO reading < 6 ppm at 12 months [72]. Following an intent-to-treat approach, participants lost to follow-up will be considered as smoking.

#### Secondary outcomes

7-day point prevalence smoking abstinence at 7-days post-quit day, and at 3- and 6-months post-intervention.Treatment satisfaction, measured with the CSQ-8 [68, 69] and the SUS [64, 65], at the end of treatment.Treatment adherence. It will be assessed to evaluate the extent to which participants use the intervention. Measures of adherence will include:
Completion of intervention components and the number of uses within each component will be obtained from the app metadata.Data obtained from the engagement subscale of the uMARS [62, 63].

For conditions with therapeutic contact, adherence will also be assessed based on the number of online sessions participants attend.

### Statistical analysis

#### Phase 1: app design

Interviews will be recorded, transcribed verbatim, and independently coded using NVivo 14 [73]. We will first develop a codebook. Initial codes will be guided by the interview guide and the original research objectives. Then, these codes will be refined, operationalized, and defined based on the raw interview data. The interviews will be coded independently by two researchers, and then iteratively revised until an intercoder reliability coefficient of at least 0.80 is achieved. Discrepancies will be addressed through continued discussion with a third researcher when needed [74, 75]. After coding is completed, we will conduct a thematic analysis to identify emerging themes.

#### Phase 2: RCT

All statistical analysis will be conducted following an intention-to-treat approach [76] in which all randomized participants will be included in the final analysis. Sociodemographic (e.g., age, sex, gender, education), tobacco-related and clinical characteristics will be reported via descriptive statistics. Parametric (χ^2^ and Student’s t) and non-parametric test (Mann-Whitney U) will be used to examine baseline differences between treatment conditions in sociodemographic variables, tobacco use, clinical variables and variables related to the use of mobile phones and apps. Given that our treatment conditions that include therapeutic contact are delivered in a group format, the primary analysis will account for clustering by treatment/contact group. The pattern of missing data will be analyzed, and multiple imputation techniques will be used based on the missingness pattern.

To analyze differences between treatment conditions, percentages of smoking abstinence (χ^2^) and effect size calculation (Cramer’s V) will be used. Due to the longitudinal nature of the collected data, statistical analyses regarding smoking abstinence outcomes will be conducted through multilevel modeling.

Moderation analysis will be conducted to examine whether treatment effects differ as a function of participant baseline characteristics, such as nicotine dependence, age, or education level. These analyses will test whether the intervention has different abstinence outcomes for specific subgroups by including treatment-condition × baseline characteristic interaction terms in the longitudinal multilevel models. We will also explore which variables could act as mechanisms of change via mediation models. Mediators will include negative affect, withdrawal symptoms, and self-efficacy.

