#### Phase 2: randomized controlled trial

##### Randomization, allocation concealment and blinding

In phase 2, participants who meet all the eligibility criteria will be randomized to one of the three groups based on a computer-generated allocation sequence (ratio: 1.1.1). Participants will not be blinded to the treatment condition, which is common in trials evaluating psychological and psychosocial interventions due to the intervention characteristics [29].

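### Baseline differences across three randomised arms are to be tested with two-group tests, and baseline cigarette dependence (FTCD) is given no prespecified main-effect role in the abstinence comparison

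*Protocol article*

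**What the plan says.** All references are to the protocol article.

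- **Baseline comparison** (Statistical analysis, Phase 2: RCT). Baseline characteristics will be summarised descriptively. In addition, chi-square, Student's t and Mann-Whitney U "will be used to examine baseline differences between treatment conditions in sociodemographic variables", and likewise in tobacco, clinical and phone or app variables. Neither analysis of variance nor Kruskal-Wallis is named.
- **Arms** (Randomization, allocation concealment and blinding). Three arms in equal ratio from a computer-generated sequence, with no stratification factor named.
- **Abstinence comparison** (Phase 2: RCT). "To analyze differences between treatment conditions, percentages of smoking abstinence (χ^2^) and effect size calculation" by Cramer's V will be used. The next sentence says that, because the data are longitudinal, "statistical analyses regarding smoking abstinence outcomes will be conducted through multilevel modeling". The primary analysis is also to allow for clustering by contact group. No main-effect covariates are listed for the multilevel model, and it is not described as unadjusted.
- **Role of dependence.** It enters as a candidate moderator, among baseline characteristics "such as nicotine dependence, age, or education level", through interaction terms in the multilevel models. The Discussion gives high nicotine dependence as an example of a specific difficulty in quitting.
- **Availability.** The FTCD "Includes 6 items to assess cigarette dependence" (Data collection). Table 1 schedules it before treatment, and completing all pre-treatment questionnaires is an inclusion criterion (Participants and study procedures).

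**The concern.** Two of the three named baseline tests do not fit a three-arm trial. To use them, the analyst must choose pairwise comparisons that the plan does not describe, and every extra pair adds false alarms. The more basic problem is that under proper randomisation any baseline difference arises by chance. A p-value then tests a hypothesis already known to be true, and says nothing about whether an imbalance matters for abstinence.

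What matters for the abstinence comparison is whether a baseline variable predicts outcome. The plan treats dependence as relevant to quitting and should have it on everyone, yet states no main-effect use of it in comparing the arms. What is at stake is a misleading baseline table and a small amount of unused precision.

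**Working it through.** **1. The plan's own figure.** Inputs from Sample size calculation: 45% versus 25%, two-sided alpha 0.05, power 90%. With pooled variance and no continuity correction, and a mean rate of 0.35:

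n = [1.960 × √(2 × 0.35 × 0.65) + 1.282 × √(0.45 × 0.55 + 0.25 × 0.75)]² / 0.20² = (1.322 + 0.845)² / 0.04 ≈ 117.4, so 118 per group.

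The plan states 120, at which power is 0.906. For 15% loss, 120 / 0.85 gives 142 and 120 × 1.15 gives 138; the plan states 140. The plan's figures are reproduced closely. They rest on an unadjusted two-proportion comparison, and nothing below changes them.

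**2. Two-group tests over three arms.** Three arms give 3 pairs. If the pairs were independent, the chance of at least one p < 0.05 under the null would be 1 − 0.95³ = 0.143. The pairs share arms, so the true figure is lower. Simulation of three pairwise t-tests with 140 per arm (20,000 runs) gives 0.121, about 12% per continuous variable. One three-group test gives 5%.

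Table 1 marks 16 instruments before treatment. Purely for illustration, take one independent continuous score from each:

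| Approach | Chance of at least one false difference |
|---|---|
| One three-group test each | 1 − 0.95^16 = 56% |
| Three pairwise tests each | 1 − (1 − 0.121)^16 = 87% |

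Both assumptions are rough. The scores will be correlated, and some variables are categorical and would go to chi-square, which handles three arms directly. The per-variable contrast of 12% against 5% is the firmer figure.

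**3. What adjustment would add.** The documents give no prognostic strength for FTCD, so a range is assumed. Logistic models with and without one standard normal covariate were simulated with 120 per arm, marginal rates held at 45% and 25%, and 3,000 runs per setting:

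| Assumed odds ratio per SD | Power unadjusted | Power adjusted |
|---|---|---|
| 1.0 (no effect) | 0.905 | 0.903 |
| 0.8 | 0.901 | 0.902 |
| 0.65 | 0.904 | 0.915 |
| 0.5 | 0.902 | 0.928 |

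The Monte Carlo standard error of each power is about √(0.9 × 0.1 / 3000) = 0.005. The gain therefore runs from nil to about 0.928 − 0.902 = 2.6 percentage points. The simulation leaves out clustering. It uses 120 rather than 140 per arm; at 140 and the same rates, unadjusted power is already 0.943, so there is less to gain.

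**The case against.** The strongest reply is that a journal article commonly leaves the covariate list of a model to the statistical analysis plan. On that view, chi-square and Cramer's V summarise crude percentages while the multilevel model carries the inference, since a plain chi-square cannot allow for clustering. This stands in large part. A reader might infer that the primary abstinence comparison is unadjusted, but the text shows that only for the chi-square. The multilevel model's covariates are unstated, which is not the same as excluded.

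Three other strong readings also fail:

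- **That all the baseline tests are unfit.** Chi-square extends to three arms, so the misfit concerns Student's t and Mann-Whitney U.
- **That baseline p-values will decide the adjustment.** The article nowhere says so. Post hoc covariate choice is a possibility left open, not something planned.
- **That leaving out FTCD biases the result or inflates type I error.** In a randomised comparison it does neither, and no stratification factor is named that would call for adjustment. Studying dependence as a moderator without giving it a stated main-effect role in the primary comparison is no contradiction.

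It can also be said that the article already promises descriptive statistics. That is true, and it means the tests can be removed without losing anything. The reply does not reach the tests themselves. They are named in the text rather than left out of it, and as named they do not suit three arms.

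**Conclusion.** The point holds as a minor one. The baseline tests named for continuous and ordinal variables do not match a three-arm design, and testing baseline differences after randomisation serves no purpose. The consequence is confined to the baseline table: about 12% false differences per variable if run pairwise, against 5% for a single three-group test.

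On adjustment, the document gives baseline dependence no prespecified main-effect role in comparing abstinence, although it should be available for every participant. Naming it is worthwhile but brings little: about 0 to 3 percentage points of power at 45% versus 25%, for assumed odds ratios of 1.0 to 0.5 per standard deviation. The validity of the primary test and the sample size of 120, 140 and 420 are untouched.

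**What to change.** 1. Remove the baseline significance tests and describe the three arms by means and standard deviations, medians and ranges, or counts, without p-values. If tests are kept, name three-group tests: analysis of variance or Kruskal-Wallis for continuous and ordinal variables, chi-square for categorical ones.
2. Prespecify the baseline FTCD score as a fixed covariate in the primary 12-month abstinence comparison, within the multilevel model that accounts for clustering by contact group. Report the unadjusted percentages and chi-square alongside. The adjusted odds ratio is conditional on FTCD, so it need not equal the crude one; the report should say so.

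The cost is a change of wording in the protocol or analysis plan, best made before outcome data are seen. No new data are needed and the sample size does not change.

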### Ethics approvals and dissemination

The study protocol, informed consent forms, and recruitment materials have been approved by the Bioethics Committee of the University of Santiago de Compostela (USC10/2025). The study will be conducted, and results will be presented in conformity with the Consolidated Standards of Reporting Trials (CONSORT) guidelines [70] and CONSORT-EHEALTH checklist [77]. Signed informed consent will be obtained from all the participants electronically. This randomized controlled trial was registered on March 21, 2025, on ClinicalTrials.gov (NCT06900985).

The results will also be disseminated to society, especially to people interested in quitting smoking, through our website (https://www.usc.gal/gl/servizos/area/seguridade-saude), social media networks (@UTTA.USC; @unidade_tabaquismo_USC; @universidade_USC), and mass media (radio, TV, written press). We also plan to disseminate the obtained results to healthcare professionals.

### Potential risks and safety

It is not expected that participants in the trial will experience harm. However, during the smoking cessation treatment, participants may experience smoking withdrawal symptoms for several weeks. Clinical psychologists and other staff at the Smoking Cessation and Addictive Disorders Unit will be available in case participants experience severe physical or mental symptoms related to the research study. All serious symptoms will be recorded and reported.

### Confidentiality and data management plan

The management of study data will adhere strictly to the provisions set forth in Regulation (EU) 2016/679 of the European Parliament and of the Council of 27 April 2016 (General Data Protection Regulation), concerning the protection of natural persons in relation to the processing of personal data and the free movement of such data. Additionally, compliance with relevant Spanish legislation will be ensured, including Organic Law 3/2018 of 5 December on the Protection of Personal Data and the Guarantee of Digital Rights, as well as Law 41/2002 of 14 November, which establishes the basic legal framework for patient autonomy and rights and obligations in the field of clinical information and documentation.

Participant data will be collected electronically using a unique identification code assigned to each individual and will be stored in password-protected folders on computers at the Smoking Cessation and Addictive Disorders Unit, University of Santiago de Compostela (Spain). All study-related data will be securely exported and stored under these coded identifiers to maintain anonymity, with personal identifiers, such as eligibility screening data and informed consent forms, kept separately from the main study records. Access to the data will be restricted to the principal investigator and authorized research staff only, ensuring strict confidentiality and data integrity throughout the trial. Individual de-identified participant data, data dictionary and statistical code will be accessible in Zenodo repository.

A data monitoring committee is not required for this research. The intervention involves minimal risks, and internal safety monitoring is included in the study procedures.

## Discussion

This study protocol presents the design of a three-arm RCT that aims to assess therapeutic treatment dose as an adjunct to a cognitive-behavioral smoking cessation treatment with an App. The study also includes an initial qualitative phase focused on user-centered app design, development, and testing to ensure the app is appealing and engaging [23].

Previous research suggests that professional support enhances adherence to digital interventions for substance use [20], thereby improving treatment outcomes. Therefore, it is hypothesized that participants in the high-intensity therapeutic contact condition will show significantly higher abstinence rates at the end of the intervention and across the one-year follow-up period compared to those receiving the low therapeutic contact condition or only the app. Despite expectations that smoking abstinence outcomes would be superior in the high-intensity contact condition, the app-only condition should be considered for its potential for broad dissemination. Self-guided mHealth interventions could be viable options because they are cost-efficient and may be especially appealing for people who smoke and are reluctant to seek traditional care or face difficulties attending therapist-guided sessions [16, 78]. In contrast, the therapist-guided conditions may be particularly necessary for individuals who experience specific difficulties quitting smoking, such as those with high nicotine dependence or with mental health conditions. We will explore possible moderators of treatment outcomes, that would allow for the identification of which individuals are most likely to benefit from each level of therapeutic contact. Finally, we will test the potential mediators to identify mechanisms by which the intervention leads to smoking cessation outcomes.

Despite its strengths, several limitations should be acknowledged. First, while the sample size is appropriate for Phase 1, it may not fully capture the diversity of user needs. Second, since participants are seeking treatment for smoking cessation, they may already have a higher motivation to quit smoking. This limits the generalizability of the results to the general population of people who smoke. Third, while the study will use CO biochemical verification to validate smoking abstinence, remote delivery has barriers, such as difficulties managing the device or downloading an additional app [79, 80]. However, to minimize the burden, we will schedule a brief video call not only to objectively assess abstinence, but also to assist participants with CO testing and to reduce the impact of these limitations. Fourth, study participants and research staff delivering the intervention will not be blinded to the treatment conditions. Although this is common in psychological studies, it may introduce social desirability and expectation biases. Finally, our trial is focused on abstinence outcomes and does not address whether the incremental cost and complexity of adding therapeutic contact provide a meaningful benefit that justifies the added costs, therapist time, and implementation complexity required to deliver it.

In conclusion, this study will contribute to the growing and rapidly evolving literature on digital health and smoking cessation. It will offer evidence on the need and dose of therapeutic contact as an adjunct to an app. Importantly, this trial may help shape efficacious, accessible, and scalable interventions to quit smoking. The study may also help clarify which intervention formats are most appropriate for different user groups, including those who may benefit sufficiently from a standalone app and those who may require additional therapeutic guidance. This is particularly relevant in real-world healthcare settings, where smoking cessation support should be tailored to users’ needs, preferences, and levels of digital literacy. Future research incorporating cost-effectiveness and implementation outcomes is warranted to determine whether lower-therapeutic contact or app-only interventions may represent viable options in healthcare settings. This could ultimately inform clinical guidelines or health policy decisions.

